## **5. TREATMENT OF SUBJECTS**

### **5.1 Investigational product/treatment**

#### **Procedural sedation and analgesia in an outpatient setting**

According to guidelines from the Health Care Inspectorate (IGZ) and Dutch Institute for Healthcare Improvement (CBO) non-anesthesiologist administered Propofol (NAAP) sedation is given and monitored by a qualified sedation practitioner [30-31]. The patient will be assessed by the sedation practitioner immediately prior to surgery on the basis of a pre-operative questionnaire. Non-invasive blood pressure, electrocardiogram and oxygen saturation are measured before vascular access is obtained. Propofol and alfentanil are used for procedural sedation.

Hysteroscopic resection is performed by an experienced surgeon by standard procedure in an office-based setting. Patients are observed after the procedure by qualified personnel and discharged as soon as all the discharge criteria are met, normally within 1 to 1.5 hours.

#### **General anesthesia**

General anesthesia can be volatile based or total intravenously, with the use of a laryngeal mask. Postoperatively, patients will be observed in the recovery room and discharged home from the clinic when all the discharge criteria are met.

The way hysteroscopic resection is performed under general anesthesia does not differ from the way it is performed under procedural sedation.

## **6. METHODS**

### **6.1 Study parameters/endpoints**

#### **6.1.1 Main study parameter/endpoint**

Primary outcome will be the percentage of complete resections, based on ultrasonography 6 weeks postoperatively by an independent gynaecologist or ultrasonographer blinded for the surgery outcome. This ultrasonography should be conducted in the follicular phase (first 14 days) of the menstrual cycle. A complete resection means that there are no signs of an intracavitary remaining of the myoma resected during hysteroscopic myomectomy on the transvaginal ultrasound.

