## SUMMARY

**Rationale:** Hysteroscopic myomectomies are performed in the majority of Dutch hospitals. The number of procedures for submucosal type 0 or I myomas between 1-3 cm performed in the operating room is estimated to be 3000 per year. Hysteroscopic myomectomy is currently performed in daycare under general anesthesia. A considerable cost reduction is expected when procedural sedation (PSA) is applied. The major contributing factors to the cost reduction are the shift from surgery in an operating theatre to an office-based setting, shorter hospital stay and outpatient care versus day care. We expect higher patient satisfaction, as hospital stay is shorter and side effects such as nausea are reduced. However, both safety and effectiveness – including the necessity for re-intervention due to incomplete resection – have not yet been fully evaluated.

**Objective:** Is hysteroscopic resection of submucous myomas under procedural sedation with propofol (PSA) in an outpatient setting a cost-effective alternative for hysteroscopic myomectomy performed under general anesthesia in the operation room?

**Study design:** non-inferiority, multicenter RCT, with a cost effectiveness analysis (CEA) alongside it.

**Study population:** patients with submucosal type 0 or I myomas (FIGO (PALM COEIN)) with a maximum diameter of 3 cm. We use a non-inferiority design: based on estimated risk of 2,5% incomplete resections in both groups, with an non-inferiority upper limit of 10%, 205 women are needed.

**Intervention:** hysteroscopic resection of submucous myomas under procedural sedation with propofol, compared to general anesthesia

**Main study parameters/endpoints:** 1) complete resection 2) costs, pain, menstrual blood loss (PBAC score), , quality of life, return to daily activities/work, hospitalization, (post)operative complications, re-interventions.

**Nature and extent of the burden and risks associated with participation, benefit and group relatedness:** Patients participating in this study are requested to complete a questionnaire at baseline, after 24 hours, 2 weeks, 8 weeks, 6 months and 12 months after the procedure. At 6 weeks after the procedure patients are asked to visit the outpatient department for a transvaginal ultrasound to assess the completeness of resection. This visit is part of the current usual care.

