#### **6.1.2 Secondary study parameters/endpoints**

Secondary outcomes are cost effectiveness, pain, menstrual blood loss (PBAC score), quality of life, return to daily activities/work, hospitalization, (post)operative complications, re-interventions. These secondary parameters will be assessed by several questionnaires.

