### **6.2 Randomisation, blinding and treatment allocation**

Randomisation will be performed web based through Alea with the use of a block design, with a variable block size. The expertise for this technology is already available for the study group (obs/gyn consortium). The study will not be double-blinded, as it is impossible to blind the health care workers and patients involved for the strategy to which the woman is allocated. The person performing the transvaginal ultrasonography at six weeks follow up, however, will be blinded for the study arm and judgement of completeness by the surgeon during the procedure. Patients will be able to complete the questionnaires online, through an link they receive by e-mail. In case patients wish to complete the questionnaires on paper, the research nurse will send the questionnaires by post at the follow-up moment.

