### **Characteristics registered during the procedure**

- completeness of resection as judged by surgeon
- surgical complications
- anesthesiologic complications (desaturation, airway obstruction, dysrhythmias, blood pressure drops, ECG alterations)
- operating time
- intravasation/fluid deficit
- recovery time (time from end of procedure until completely awake and communicative)
- use of pain medication and dose
- pain intensity measured by VAS scores
- duration of hospitalization (hours)

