### **Questionnaires**

Participating women will fill in questionnaires at baseline, which will be given before the surgical procedure. During follow-up, patients will fill in questionnaires at 24 hours, 2 weeks, 8 weeks, 6 and 12 months after randomisation. Questionnaires will contain:

- Short questionnaire on side effects 24 hours after surgery.
- the EuroQoL (EQ-5D-5L) questionnaire (15 questions) to assess the quality of life
- PBAC scores to assess the amount of menstrual blood loss
- Uterine Fibroid Symptoms – Quality of Life (UFS-QoL) questionnaire (37 questions) to assess the quality of life focussing on patients suffering from uterine fibroids
- Recovery Index (RI-10) questionnaire (10 questions): to assess the patients' recovery process

- Medical Consumption Questionnaire (iMCQ)[32]: for cost effectiveness analysis
- Productivity Cost Questionnaire (iPCQ)[33] to assess productivity loss
- Short questionnaire on recurrence and re-interventions at 12 months after surgery.

|           | Side effects
Pain
(VAS) | EQ-5D-5L | PBAC | UFS-QoL | RI-10 | iMCQ | iPCQ | Re-intervention |
|-----------|-------------------------------|----------|------|---------|-------|------|------|-----------------|
| Baseline  |                               | X        | X    | X       |       |      |      |                 |
| 24 hours  | X                             | X        |      |         | X     |      |      |                 |
| 2 weeks   |                               | X        |      |         | X     |      |      |                 |
| 8 weeks   |                               | X        | X    | X       | X     | X    | X    |                 |
| 6 months  |                               |          |      |         |       | X    |      |                 |
| 12 months |                               | X        | X    | X       |       | X    |      | X               |

A patient preference study (for which a different study protocol will be created) will be conducted alongside the trial including evaluation of patient satisfaction.

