## 8. STATISTICAL ANALYSIS

### 8.1 Data analysis and presentation/synthesis

Primary analysis will be by intention-to-treat. We will also perform a per protocol analysis, given the non-inferiority design of the study, where crossover between the groups will increase the chances of concluding non-inferiority, if in reality the treatment is not-inferior. We will present the percentage of complete resections at 6 weeks in both groups, with according relative risks and 95% confidence interval. Differences will be tested with the chi-square test, or, if the expected cell count is low using the Fisher exact test. We will also calculate the relative risk, adjusted for center where the procedure has been performed. Complications during and after surgery, and re-interventions will be categorized and evaluated by a Clinical Evaluation Committee, independent and blinded for the type of surgery performed (where possible). Average pain intensity during the procedure as well as the highest pain intensity during the procedure will be reported as means with SD, risk differences between both groups will be calculated with according 95% confidence interval. Time to recovery and pain will be visualized in a graph, and analyzed using a mixed model, that can take into account repeated measures in the same woman over time. The quality of life and PBAC scores will be analyzed according the developed algorithms. We will perform a subgroup analysis for myoma size (<2 cm versus  $\geq 2$  cm) and for parity (nulliparous versus multiparous women).

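### The primary endpoint is scored only from the 6-week scan, so an incomplete resection redone before the scan counts as complete; this favours non-inferiority if early repeats remove more failures from the sedation arm

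*Protocol*

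**What the plan says.** Section 6.1.1 sets the outcome and its timing: "Primary outcome will be the percentage of complete resections, based on ultrasonography 6 weeks postoperatively". It then defines success: "A complete resection means that there are no signs of an intracavitary remaining of the myoma resected during hysteroscopic myomectomy on the transvaginal ultrasound". Section 6.3 (Completeness of resection) repeats the scan-based assessment and adds contrast sonography when the scan is inconclusive. Neither section limits success to a single procedure, and neither says whether the 6 weeks run from the first or from a repeat procedure.

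Three other provisions matter:

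- Section 6.3 lists "completeness of resection as judged by surgeon" among the items registered during the procedure, but this does not enter the endpoint.
- Under section 6.2 the person doing the scan "will be blinded for the study arm and judgement of completeness by the surgeon during the procedure".
- Section 6.1.2 places re-interventions among the secondary outcomes: "hospitalization, (post)operative complications, re-interventions. These secondary parameters will be assessed by several questionnaires". The scheduled instrument in section 6.3 is a "Short questionnaire on recurrence and re-interventions at 12 months after surgery".

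The Summary, and section 1 in similar words, list "the necessity for re-intervention due to incomplete resection" as part of what has not yet been fully evaluated.

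Section 8.1 makes intention-to-treat primary and adds a per-protocol analysis on the ground that "crossover between the groups will increase the chances of concluding non-inferiority, if in reality the treatment is not-inferior". It does not say who belongs to the per-protocol set.

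**The concern.** The trial asks whether resection under sedation is completed as often as under general anesthesia. A first procedure that fails and is soon redone is a failure on that question. Under the written definition it becomes a success once the repeat has cleared the cavity. The assessor is properly blinded and cannot detect it, and the surgeon's own judgement is recorded but not used.

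The error to guard against here is a false claim of non-inferiority. If early repeats are more common after sedation, the scan-only rule removes failures mainly from the sedation arm and narrows the observed difference. Very few events decide the result, so a few reclassified women can matter.

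The per-protocol analysis is the natural second check, but its stated reason is reversed. Crossover makes the arms alike. If sedation is truly non-inferior, a conclusion of non-inferiority is correct and no harm is done. The danger arises when sedation is in reality inferior.

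**Working it through.** **Inputs.** Section 4.4 gives 205 randomised, 90% power, 2.5% incomplete in both groups, a margin of 7.5 percentage points, alpha 0.025 and 10% drop-out. I assume 1:1 allocation and one-sided alpha, neither of which is stated. The share of failures redone before the scan is not in the protocol; I write it as *f* and vary it.

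**The plan's own figure.** With the unpooled normal formula,

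n per arm = (1.960 + 1.282)² × (2 × 0.025 × 0.975) / 0.075² = 10.507 × 0.04875 / 0.005625 = 91.06, rounded up to 92.

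Total 2 × 92 = 184; 184 / 0.9 = 204.4, rounded up to 205. The stated size reproduces.

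**How few events decide.** Expected failures are 92 × 0.025 = 2.3 per arm. Under a Farrington-Manning test with 92 per arm, margin 0.075 and one-sided 0.025, two failures under general anesthesia allow non-inferiority with three sedation failures but not with four.

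**Effect of early repeats.** Put the truth at the margin: first-procedure failure of 10% under sedation and 2.5% under general anesthesia. Non-inferiority is then false, and declaring it is the error that alpha should limit. If a share *f* of failures is redone successfully before the scan, the scan sees 10% × (1 − f) under sedation. Under general anesthesia it sees 2.5%, or 2.5% × (1 − f) if the same share is redone there. The probability of declaring non-inferiority is the sum of the binomial probabilities of all outcome pairs that pass the test:

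| Share redone, *f* | Sedation failure seen | P(non-inferiority), repeats in sedation arm only | P(non-inferiority), same share in both arms |
|---|---|---|---|
| 0 | 10% | 2.1% | 2.1% |
| 5% | 9.5% | 2.9% | 2.6% |
| 10% | 9.0% | 3.9% | 3.3% |
| 25% | 7.5% | 9.1% | 6.4% |
| 50% | 5.0% | 30.9% | 18.2% |

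The last column exceeds 2.1% because an equal share of unequal failure rates still shrinks the absolute difference. If repeats instead removed the same number of percentage points from each arm, the difference would be unchanged and the bias about nil.

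**Would per-protocol reveal it?** Only its membership rule can settle this. If it excluded women redone under general anesthesia, and all repeats were of that kind, sedation failure would read 0.10(1 − f) / (1 − 0.10f). At f = 25% this is 0.075 / 0.975 = 7.7%; at f = 50% it is 0.05 / 0.95 = 5.3%. Both are close to the intention-to-treat readings of 7.5% and 5.0%, and well below the true 10%. A woman redone under sedation is no crossover. She would probably stay in the set and count as complete.

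**The case against.** **The pathway is narrow.** To be miscounted, a failed procedure must be recognised, rescheduled and redone before the 6-week visit, and the protocol describes no such repeat. A failure not redone by then would normally still show a remnant and be scored incomplete. This stands, and it is why the low rows of the table matter as much as the high ones.

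**The rule treats both arms alike.** Its direction depends on where repeats occur, and the protocol gives no repeat or conversion rate for either arm. This stands.

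**Repeats are not ignored.** Re-interventions are a secondary outcome, and section 8.1 has an independent committee, blinded where possible, evaluate them. An excess in one arm would be reported. That is true, but it would not change the primary conclusion.

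**Scoring the 6-week state of the assigned strategy is a recognised choice.** It is, but it answers a different question from the one raised in the Summary, and the protocol does not say that it was chosen deliberately.

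**A stronger reading is tempting:** that the per-protocol set drops these women, so that both analyses err in favour of sedation. The protocol does not support this. The set is undefined, and its membership is a matter that an analysis plan commonly settles. The crossover rationale makes exclusion of women moved to general anesthesia a natural reading, but no more than that. The direction of the intention-to-treat error is likewise conditional.

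**Conclusion.** The gap is real, and it lies in the endpoint definition that the protocol itself fixes. As written, an incomplete or abandoned index resection redone before the scan counts as complete in the allocated arm. It biases toward non-inferiority if early repeats remove more failures from the sedation arm.

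Its size is an assumption, not a finding. With 92 per arm and true failure at the margin, the false-positive probability rises from 2.1% to between 2.9% and 3.9% if 5% to 10% of sedation failures are redone, to 9% at a quarter (6% if the same share is redone in both arms) and to 31% at half (18%). If early repeats are rare, the effect is small.

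The per-protocol analysis could fail to reveal the problem, depending on a membership rule not given here. The reversed rationale in section 8.1 is an error on the page whatever the repeat rate. The first half of that clause, that crossover makes a conclusion of non-inferiority more likely, is right; the condition attached to it is not.

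**What to change.** **Section 6.1.1.** State that the 6 weeks run from the index procedure, and add: *Any second resection of the index myoma before the 6-week ultrasound counts as incomplete resection, whatever the scan shows.*

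**Data collection.** Record the date of any repeat procedure at the 6-week visit. The scheduled re-intervention questionnaire comes only at 12 months and may not date an early repeat against the scan.

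**Section 8.1.** Change the last word of the crossover clause to *inferior*. State that women are not excluded from the per-protocol sedation group because their sedation procedure was abandoned, converted or repeated, and add a supportive analysis that counts them as failures.

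**Cost.** The change is wording plus one dated data item, with no change to care, and should be made before outcome data are seen. The downside is that the complete-resection rate, and so the power, may look less favourable. The loss is slight if early repeats are rare. It is not slight if they add a full point of failure in the sedation arm only: with 3.5% v 2.5%, SE = √[(0.035 × 0.965 + 0.025 × 0.975) / 92] = 0.0251. Power is then Φ(0.065 / 0.0251 − 1.96), about 73% instead of 90%, and 90% power would need 323 women. The sample size should be rechecked with an explicit repeat rate.

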#### **6.1.2 Secondary study parameters/endpoints**

Secondary outcomes are cost effectiveness, pain, menstrual blood loss (PBAC score), quality of life, return to daily activities/work, hospitalization, (post)operative complications, re-interventions. These secondary parameters will be assessed by several questionnaires.

### **6.2 Randomisation, blinding and treatment allocation**

Randomisation will be performed web based through Alea with the use of a block design, with a variable block size. The expertise for this technology is already available for the study group (obs/gyn consortium). The study will not be double-blinded, as it is impossible to blind the health care workers and patients involved for the strategy to which the woman is allocated. The person performing the transvaginal ultrasonography at six weeks follow up, however, will be blinded for the study arm and judgement of completeness by the surgeon during the procedure. Patients will be able to complete the questionnaires online, through an link they receive by e-mail. In case patients wish to complete the questionnaires on paper, the research nurse will send the questionnaires by post at the follow-up moment.

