### **4.4 Sample size calculation**

The study is designed as a non-inferiority study, in which we want to investigate if hysteroscopic myomectomy under procedural sedation with propofol is non-inferior to the same surgical procedure under general anesthesia. With 205 women randomized we have 90% power to demonstrate non-inferiority, based on an estimated 2,5% incomplete resections in both groups, with an non-inferiority upper limit of 10% incomplete resections defined as non-inferior (i.e. a delta of 7.5%), an alpha of 0.025 and a drop-out rate of 10%.

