### **Characteristics registered after the procedure**

Nausea and vomiting, sore throat, pain (VAS score)

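### Posting paper questionnaires at the follow-up moment cannot work for the 24-hour form, so women who choose paper would answer it late or from recall

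*Protocol*

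**What the plan says.** Section 6.2 sets the mode of collection. The default is electronic: "Patients will be able to complete the questionnaires online, through an link they receive by e-mail". For women who wish to use paper, "the research nurse will send the questionnaires by post at the follow-up moment".

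Section 6.3, under Questionnaires, sets the moments: "patients will fill in questionnaires at 24 hours, 2 weeks, 8 weeks, 6 and 12 months after randomisation". One listed item is a "Short questionnaire on side effects 24 hours after surgery". In the schedule table, the 24-hour row marks side effects with VAS pain, EQ-5D-5L and RI-10. Side effects and VAS pain are marked in no other row. EQ-5D-5L and RI-10 are next due at 2 weeks.

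Only the baseline forms are described as handed over in advance: "Participating women will fill in questionnaires at baseline, which will be given before the surgical procedure".

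Outside the questionnaires, section 6.3 also lists VAS pain, analgesic use and recovery time among the items registered during the procedure. It lists nausea and vomiting, sore throat and VAS pain among those registered after it, without a time point.

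**The concern.** The posting rule is harmless at 2 weeks or later, where a few days matter little. At 24 hours the delivery delay is as long as the interval being measured, or longer. A woman on paper who follows the protocol exactly cannot give an answer at 24 hours. She gives a later answer, or a recollection, that is filed under the 24-hour label.

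This is also the stage of recovery at which the protocol expects sedation to differ from general anesthesia: the Summary and section 1 anticipate less nausea and quicker recovery. Section 8.1 plans a repeated-measures mixed model for pain and time to recovery. The protocol mentions no record of when a form was completed, so a late answer might not be recognisable as late. An analysis plan could not repair this, because it cannot recover an answer that was not collected at the intended time.

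**Working it through.** **1. Can both rules be followed?** The protocol gives no figure on this point to reproduce, so the check is to read the sections together.

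- Paper forms leave the hospital at the follow-up moment (section 6.2).
- The first follow-up moment is 24 hours (section 6.3).
- Hand-over in advance is described for baseline only (section 6.3).
- No section describes hand-out at discharge, advance mailing or telephone collection for the 24-hour form.

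The 24-hour form therefore reaches a paper user after the time it is meant to describe.

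**2. How late?** The postal delay is not in the protocol. Assuming 1 to 3 days, arrival is at 24 + 24 × 1 = 48 hours to 24 + 24 × 3 = 96 hours.

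**3. How many women?** The paper share is not stated. Assuming 2% to 30% of the 205 women in section 4.4: 205 × 0.02 = 4.1 and 205 × 0.30 = 61.5, so about 4 to 62 women.

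**4. What could it do to a 24-hour arm difference?** Suppose paper answers describe the day of completion and the arm difference halves every h days. With paper share q and delay d days, the proportional shrinkage is q × (1 − 0.5^(d/h)).

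| q | d = 1, h = 2 | d = 3, h = 1 |
|---|---|---|
| 0.02 | 0.6% | 1.8% |
| 0.10 | 2.9% | 8.8% |
| 0.30 | 8.8% | 26.3% |

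None of q, d and h comes from the protocol. The table shows sensitivity to assumptions and is not an estimate of bias.

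**5. QALYs.** EQ-5D-5L is scheduled at baseline, 24 hours, 2 weeks, 8 weeks and 12 months. Assume a simple area under the curve with baseline at day 0. The 24-hour value then carries a weight of (14 − 0)/2 = 7 days. An illustrative utility error of 0.1 gives 0.1 × 7/365 = about 0.002 QALY per paper user. Averaged over all women at 30% paper use, this is 0.30 × 0.002 = about 0.0006. If both arms are affected alike, it largely cancels in the difference.

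**6. Primary comparison.** Section 4.4 assumes 2.5% incomplete resections in both groups, a margin of 7.5%, alpha 0.025, 90% power and 10% drop-out. Then 2 × 0.025 × 0.975 × (1.960 + 1.282)² / 0.075² = 91.06, so 92 per arm and 184 in total; 184/0.9 = 204.4, rounded up to 205. The stated figure reproduces and does not depend on the questionnaires.

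**The case against.** The best reply is that this is a strict reading of loose logistics wording. The follow-up moment may mean around that time, and sites could solve the problem in their instructions. Online is the default, and the questionnaires serve secondary outcomes only. The literal timing also depends on a clock that the protocol leaves unclear. Section 6.3 counts from randomisation, under which a 24-hour form could be posted before surgery. The Summary counts from the procedure, and the side-effect item counts from surgery.

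Much of this stands and limits the weight of the point. It does not remove it. Postal forms around the due time suit every moment except 24 hours, and on the surgical clock, the only one on which a side-effect form makes sense, the stated route fails. The unclear clock is a further reason to amend the text.

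A reader might infer more than the documents support:

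- **That the 24-hour value is lost for every paper user.** The form asks about side effects 24 hours after surgery and can be answered from recall. Such an answer is less precise, but it is not absent.
- **That early pain and side effects have no other source.** VAS pain, nausea, vomiting and sore throat are also registered outside the questionnaire list. Because no time point is given after the procedure, these records do not clearly replace the 24-hour form, and they do not cover EQ-5D-5L or RI-10.
- **That the pain model will contain a wrong time.** Section 8.1 does not say whether nominal or actual time enters. That choice is commonly left to the analysis plan, which is not shown.
- **That the arm difference is pulled toward zero by a known amount.** Shrinkage follows only if answers describe the day of completion; recall can err in either direction.

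**Conclusion.** The point holds as a minor one. The posting rule in section 6.2 cannot deliver the 24-hour form in section 6.3 on time, and paper users would answer it a day or more late or from recall. What is exposed is the 24-hour side-effect and VAS pain questionnaire, RI-10 and EQ-5D-5L in those women.

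The size is not determined by the protocol. The figures of 4 to 62 women and 48 to 96 hours rest on an assumed paper share of 2% to 30% and an assumed delay of 1 to 3 days. The direction of any bias is not established. The QALY effect is negligible, and the primary endpoint, sample size and non-inferiority conclusion are untouched. The case for acting is that a stated rule fails at one time point and the remedy costs almost nothing.

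**What to change.** Amend section 6.2 as follows:

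- Give women who choose paper the 24-hour form before they go home, with an instruction to complete it 24 hours after the procedure and a field for the date and time of completion.
- Post the later paper forms so that they arrive by the due date.

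At the same time, reconcile the reference time of the questionnaire schedule between the Summary (procedure) and section 6.3 (randomisation, with surgery for the side-effect item).

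The cost is a short text change and one extra item to hand over at discharge. No treatment, endpoint or sample size changes.
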